## Abstract

**Background:**

Young mothers living in low-income urban settings often are exposed to significant and chronic environmental difficulties including poverty, social isolation and poor education and typically also have to cope with personal histories of abuse and depression. Minding the Baby® (MTB) is an interdisciplinary home-visiting programme developed to support first-time young mothers, which integrates primary care and mental health approaches into a single intensive intervention from the last trimester of pregnancy until the child’s second birthday. The primary aim of the intervention is to promote caregiver sensitivity, and, secondarily, to promote both child and maternal socioemotional outcomes.

**Methods/design:**

This is a multisite randomised controlled trial (RCT) with a target recruitment of 200 first-time adolescent mothers (under 26 years of age). One hundred participants will be randomised to the MTB group and they will receive the MTB programme in addition to the usual services available in their areas. Those participants not allocated to MTB will receive Treatment as Usual (TAU) only. Researchers will carry out blind assessments at baseline (before the birth of the baby), and outcome assessments around the child’s first and second birthdays. The primary outcome will be the quality of maternal sensitivity and the secondary outcomes will focus on attachment security, child cognitive/language development, behavioural problems, postponed childbearing, maternal mental health and incidents of child protection interventions.

**Discussion:**

This study evaluates the Minding the Baby® programme in the UK. In particular, this RCT explores the effectiveness of this integrative approach, which focusses on maternal mental issues as well as parent-infant interaction, parental concerns and developmental outcomes.

**Trial registration:**

ISRCTN08678682 (date of registration 3 April 2014).

**Electronic supplementary material:**

The online version of this article (doi:10.1186/s13063-016-1618-4) contains supplementary material, which is available to authorized users.

## Background

### Overview and rationale

The NSPCC, in collaboration with University College London, the University of Reading, the Yale Child Study Centre and the Yale School of Nursing, is initiating a multisite study of the effectiveness of a targeted prevention programme that incorporates well-established principles of home visiting with a more comprehensive package of care for the developing mother-infant relationship. The programme represents an important opportunity to advance the UK’s provision of evidence-based support for at-risk families and to intervene effectively in the intergenerational cycle of disadvantage. The Minding the Baby® (MTB) programme is an interdisciplinary intervention that was developed and tested by a team of researchers and clinicians at the Yale Child Study Centre and the Yale School of Nursing [1]. MTB combines many of the benefits of home-visiting programmes – particularly their relative cost-effectiveness, client acceptability and accessibility – with a coherent, evidence-based clinical dimension that is informed by, and directly targets, well-studied mechanisms of risk in early child development. In focussing on key domains of parent-child relationships where disturbances are known risk factors for later child maladjustment, particularly the sensitivity of parental care, the security of infant-parent attachment and the parent’s capacity to reflect on the child as an autonomous agent with needs, feelings and thoughts, the programme aims to combine best clinical practice in early prevention with scientific evidence regarding the developmental processes that promote optimal child outcomes. Currently, the UK health and social care systems offer a range of services to young families targeting mental health or promoting family relationships from birth, which are not always evidence-based and vary considerably from region to region. Home-visiting programmes are characterised by the presence of consistent and reliable support figures with high-quality training who are capable of addressing a broad range of parenting concerns from the practical to the emotional [2]. The highly influential Nurse Family Partnership (NFP) model is a well-known example that has been found to be effective for several important early child and maternal outcomes [3]. A notable limitation of existing home-visitation programmes, however, is the relative lack of focus on supporting parent-child interaction and particularly attachment. This is a central target of MTB [4, 5]. Longitudinal outcome studies clearly show that disturbances in the quality of care can have lasting negative consequences for children’s development, and the long-term social and financial costs associated with these poor outcomes are likely to be considerable [6]. The potential value of effective early intervention focussed on sensitivity of care, particularly for parents experiencing multiple social adversities, therefore, cannot be overstated.

This randomised clinical trial will test the hypothesis that an intensive home-visiting programme focussed on promoting young parents’ sensitive attunement to their infants and their ability to mentalise on their baby’s thoughts, feelings and needs, will lead to improvements in the sensitivity of parenting of children age 2 years compared to parents who receive routine care. The study will also examine several secondary hypotheses, including that the programme will increase offspring rates of secure attachment, improve cognitive and behavioural outcomes and promote maternal mental health.

### Background and significance

Although rates of teenage pregnancies have been dropping in the UK over the last 10 years, it remains the case that such pregnancies are greatly over-represented in low-income urban populations [7]. The many environmental stressors that these young parents face (poverty, single parenthood, social isolation and poor educational achievement [8]) are often amplified by personal histories of abuse, depression and posttraumatic stress disorder (PTSD) [9, 10]. These parents may find themselves not only having to deal with their own developmental needs but also trying to take on the complex roles and responsibilities of parenting. It is perhaps not surprising that young parents living in these circumstances are more susceptible to mental health problems and may struggle to become responsive nurturing parents [11, 12]. Social disadvantage more generally represents a broad but very reliable marker of a host of contextual, psychological and developmental risk factors that have well-established negative impacts on the quality of parenting and on child development [13–15]. The MTB programme is aimed at supporting young parents facing multiple social stressors, and raising their first infant in adverse social circumstances, in order to promote positive parenting, raise rates of secure attachment and improve child developmental outcomes.

The MTB programme is the result of an interdisciplinary collaboration between the Yale School of Nursing and the Yale Child Study Centre. MTB is an intensive and preventive home-visitation programme for young first-time parents. MTB primarily evolved from two home-visiting models that originated in the US; the NFP and the infant-parent psychotherapy model. David Olds and colleagues developed the NFP programme [3], which involves home visits by highly trained nurses to vulnerable high-risk first-time mothers. Home visits begin at the end of the second trimester of pregnancy and continue through the child’s second birthday. Extensive research on the effectiveness of the NFP programme in high-risk populations showed improved health, parenting and developmental outcomes [2, 3, 16–23]. A different emphasise is on the infant-parent psychotherapy model which was developed to protect infants and help parents with mental health problems, often as a result of ongoing trauma. Although this model has been less rigorously tested than the NFP programme, positive child outcomes were found. In particular, this programme appears to supports the development of healthy mother-child relationships and secure attachment [24], both of which are prognostic indicators of longer-term positive developmental outcomes in the child [25].

The MTB programme brings together both these models, providing a holistic intervention that not only addresses maternal mental health issues but also health, attachment and life course outcomes for mother, child and family. Thus, MTB aims to bring together health, developmental, attachment and mental health approaches. By incorporating both nursing and mental health approaches, MTB serves to address some of the more complex needs of mothers and families at risk.

### Attachment and Reflective Functioning

It is firmly established in the attachment field that the quality of the infant’s attachment to their primary caregiver is robustly related to a range of child outcomes [5]. MTB builds on this evidence and makes the promotion of secure attachment a primary clinical objective as a means of bringing about positive changes in the infant’s social, emotional and cognitive development. Originally, Ainsworth and colleagues [26] suggested that a mother’s ability to respond sensitively to her child’s cues would be crucial for the development of secure mother-infant attachment. Later research [27] empirically tested this hypothesis and found broad support for the role of sensitivity in secure attachment. Furthermore, recent work has highlighted the role of the mother’s own mental state with respect to attachment – referred to as her internal working model (IWM) of attachment, in shaping the sensitivity of care, and thus her child’s attachment security [28]. These attachment representations are thought to shape how a parent perceives their child and, accordingly, how they respond to the child’s behaviour, cues and communications [29].

A critical feature of the way in which parents think about their children is their ability to consider the child’s thoughts, feelings and beliefs, and to treat the child, therefore, as an individual with a mind. Crucially, research indicates that this ability not only to think of the child as an individual with their own thoughts and feelings, but also to understand and make a causal connection between the child’s behaviours and their underlying feelings and experiences, is crucial in the development of a secure attachment [30]. This capacity has been termed by [name] and colleagues as ‘mentalisation’ or ‘Reflective Functioning’ (RF) [31]. Slade and colleagues’ research in this area has demonstrated consistent relationships between a mother’s ability to mentalise, maternal behaviour, and child attachment [30, 32].

The MTB programme is rooted in this developmental theory and, at its core, the MTB programme aims to increase the parent’s capacity to think about their child and reflect upon their thoughts, and feelings, and to respond in a sensitive and attuned way to the child’s cues and communications.

### Minding the Baby®: an interdisciplinary approach

The home-visiting intervention programmes presented above have mostly focussed on either the practical aspects of parenting or the quality of the mother-child relationship and attachment. MTB aims to address both these elements of parenting.

The UK MTB clinical team includes two qualified practitioners: a nurse or health visitor and a social worker who are both highly trained and supervised in particular techniques and developmental approaches tailored for working with vulnerable young mothers. The nurse provides advanced levels of practical parenting support including individual and family health assessments, nutritional advice and family planning. The social worker provides mental health support to mother and baby, in-home assessment and intervention for mild to moderate mental health problems like depression, anxiety and PTSD symptoms that the mother might be affected by. Crucial to the success of the MTB programme is the mother’s relationship with the MTB practitioners. Their engagement and fostering of ongoing relationships with these at-risk, first-time young mothers, as well as having the professional expertise that matches their complex health, social and mental health needs, is aimed to diminish attrition from the programme. This kind of integrative model is considered to be crucial for maximising both parental and child outcomes across a range of domains.

Following the Yale model, the UK MTB is grounded in well-established developmental research, builds on the experience of similar successful programmes, is a relationship-based model, delivers a flexible model of care design to match the varying and often complex needs of at-risk families, and has a robust, manualised system of training and supervision.

### Aims and objectives

Aim 1: the primary aim of this study is to test whether participation in the MTB programme leads to improvements in the quality of parenting and specifically the degree of maternal sensitivity.

Aim 2: the secondary aims of the study are to measure the effects of the MTB programme in relation to (1) maternal outcomes including maternal mental health, maternal RF and postponed subsequent child bearing and (2) infant outcomes including incidents of child protection intervention, attachment security to the parent, cognitive and language development and behavioural problems.

Aim 3: a further key secondary aim is to assess the cost benefit/cost-effectiveness of the MTB programme in order to sustain future programmes.

## Methods

### Design

This is a multisite randomised controlled trial, with randomisation at the case level. This trial will utilise a two-arm design, with random allocation to either MTB plus Treatment as Usual (TAU) or a TAU-only control condition. Allocation will be by minimisation, controlling for maternal age, maternal depression and study site. Figure 1 shows a flow diagram of the study design, and the Standard Protocol Items: Interventions for Reporting Trials (SPIRIT) checklist is presented in Additional file 1 [33, 34].

**Fig. 1 Fig1:**
[figure not shown]
Flow diagram of the study design

### Outcome measures

#### Primary outcome

The primary outcome is the quality of parenting, operationalised as maternal sensitivity [26]. Maternal sensitivity will be measured at ages 1 and 2 years and will be treated as a continuous score, with both time points included in the primary analysis.

In order to measure parenting sensitivity at ages 1 and 2 years, we will use several short tasks from our existing studies of attachment and another ongoing clinical trial. The first task focusses on mother-infant interaction in the context of free-play. Known as the ‘three-boxes procedure’, the mother shows the child experimenter-provided toys in three containers in a set order [35–37]. The second is a procedure pioneered by Smith and Pederson [36]. In this task, mother and infant are left to explore a relatively empty room, while the mother must also complete a distraction questionnaire. Another task involves brief observations, one focussing on book-sharing and the other on a difficult-to-manipulate toy. Finally, we are using a separate joint book-reading observation in which the content of the book involves strong attachment-related scenarios. In each case, maternal sensitivity will be rated, using Emotional Availability Scales [38], an observation tool. The scales describe and assess four dimensions on the adult side (sensitivity, structuring, nonintrusiveness and nonhostility) and two dimensions on the child side (responsiveness and involvement with the caregiver). Dimensions are measured on a scale, with scores of between 1 and 7. Scales will be standardised and summed to yield a total score across all tasks for the main analysis. The use of specific contexts for mother-infant interactions will also allow us to determine whether the intervention is changing the particular processes associated with each domain of child development in tertiary analyses.

#### Secondary outcomes

*Child attachment security*, measured with the Attachment Q-Set (AQS: [39]), which will be administered at year 2. The AQS is based on a set period of observation of children aged 1–5 years in the home environment. The AQS consists of a set of 90 cards with a specific behavioural characteristic described on each card that is age-appropriate. The cards are used as a standard vocabulary to describe the behaviour of a child in a home setting, with an emphasis on secure-base behaviour. The researcher who has observed the parent and child ranks the cards into several piles from ‘most descriptive of the subject’ to ‘least descriptive of the subject’. The Q-Set provides a score along a continuum of secure to insecure. The Q-Set has shown good convergent and discriminate validity [40] and is a strong predictor of later developmental outcomes [41].

*Child cognitive and language development* will be assessed at year 2 using the Bayley Scales of Infant and Toddler Development, third edition (Bayley-III) [42]. The Bayley-III is an individually administered assessment that evaluates the child’s mental and motor development. The scales are administered when children are between the ages of 2 months and 42 months. This yields two separate continuous scales representing overall cognitive development and language development. The Bayley-III is a standardised instrument and the cognitive scales and language composite correlate, respectively (*r* = .79) and (*r* = .82), with the WPPSI-III Full-scale IQ (Weschler Preschool and Primary Scale of Intelligence), reported for children aged 28–42 months. Bayley-III is also UK-validated [43].

*Behavioural problems* will be assessed with the Child Behaviour Checklist (CBCL: [44]) questionnaire at year 2. This consists of a 100-item parent-report questionnaire and is valid for children from 18 months and older. The CBCL measure yields three age-normed scales of Internalising Problems (i.e. anxious, depressive, and over-controlled), Externalising Problems (i.e. aggressive, hyperactive, noncompliant, and under-controlled) and Total Problems. Parents record responses with: 0 (Not true, as far as I know), 1 (Somewhat or Sometimes true) or 2 (Very true or Often true). The analysis will focus on the Total Problem scale. The CBCL is one of the most widely-used standardised measures in child psychology for evaluating maladaptive behavioural and emotional problems [45].

*Postponed child-bearing* will be assessed at each follow-up when mothers will be asked about their pregnancy status. The number of months from baseline to the next pregnancy will be used for analysis.

*Maternal mental health* will be measured with the Edinburgh Postnatal Depression Scale (EPDS: [46]) questionnaire which will be administered at baseline, year 1 and year 2. The EPDS is a 10-item questionnaire screening for postnatal depression. Mothers’ responses are on a scale of 0 to 3, and a score is calculated adding individual items. All three total scores from the questionnaire will be entered into the analysis, with change from baseline being the outcome of interest. EPDS is a well-validated measure of depression [47] that may be used within 8 weeks postpartum but has also been applied for depression screening during pregnancy [48].

*Child Quality of Life* will be assessed at year-1 and year-2 follow-ups with the Warwick Child Health and Morbidity Profile (WCHMP) questionnaire [49]. This consists in a 10-item survey where parents are asked to report on health and morbidity in infancy and childhood. The WCHMP has shown to be reliable and valid with low interobserver variation [49]. An incremental cost-effectiveness ratio (ICER) will be calculated and the two groups of mothers compared.

*Health and social care resource use* will be collected throughout the study using the Service Use and Supports Questionnaire (SUS) [50]. This is a self-report questionnaire administered at baseline and every subsequent follow-up, i.e. 6 months, year 1, 18 months and year 2. Mothers are asked to note whether they had any input from professionals and voluntary agencies in the previous 6 months, in four areas: (1) health services, (2) mental health services, (3) support services and (4) child care services. Parents are also asked to note down the single most helpful service they have accessed over the previous 6 months. Costs are applied to service use at each time point. Total costs per patient will be calculated from the total across all follow-up points and adjusted for by baseline values. Unit costs will be obtained from the Personal Social Services Research Unit’s (PSSRU) nationally published reference costs and published studies.

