#### Treatment as Usual (TAU)

TAU will be the standard care available in the local community, which will be determined by the needs of each family and the local service provision. The first line of services is provided at the primary care level by universally available professionals such as GPs, health visitors and midwives. For individuals who require more support after birth the help they can receive will vary depending on where they live and the degree of their needs. In general, TAU is often a package of support from family support workers, enhanced health visiting, social worker or midwifery services (listening visits), one-to-one support from clinical psychologists (provided through local CAMHS services), psychotherapists or counsellors, postnatal support groups, crèches providing respite, parenting education workshops, peer-supported groups, home-visiting services, child psychiatry and family therapy. The Service Users and Support (SUS) questionnaire will be used to check what usual care services both groups of participants receive during the trial.

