### Intervention fidelity

Adherence to the MTB intervention protocol will be achieved in close collaboration with the Yale team (including the primary developers) in the following ways:All participant contact will be guided by the written intervention manual as well as other training materialsAll clinicians will receive extensive training in the MTB model via in-person, taped, or videoconference training sessions led by the Yale MTB trainers. The Yale MTB trainers include senior nurse and mental health supervisors and home visitorsAll MTB practitioners will record detailed information regarding their direct and indirect contact with familiesIn order to ensure that home visits adhere to the Yale MTB intervention programme after each visit practitioners will complete a Home Visit Form. This aims to describe the visits in detail and compare them with the US MTB intervention home visits. In particular practitioners record the length, nature and focus of the visit and the families’ level of engagement. It also summarises the focus of the visit, e.g. parenting, health, mental health, etc., and the time spent on each topicSpecially trained supervisors will undertake model fidelity monitoring by random sampling of families at each site and discussing the outcomes with the relevant sites at compliance visitsAll practitioners receive regular supervision by Yale-trained local UK supervisors. These specially trained supervisors meet monthly via phone with the Yale MTB trainersRegular disciplinary and interdisciplinary supervision will be provided by specially trained supervisors and the Yale MTB team (in addition to supervision provided as usual by the practitioners’ line managers)

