### Additional data analysis

#### Economic evaluation

We will conduct a cost-effectiveness analysis of MTB relative to the control condition from a broad societal perspective.

Cost information: we propose two elements to the cost component of the cost-effectiveness analysis:Cost of MTB: this will include fixed costs associated with the resources required to run the service as well as variable costs associated with training, staffing and related consumables. We will calculate a bottom-up costing of the service and calculate a weighted cost per case based on the caseload of each practitionerCosts of the use of other resources: we will use a self-completed Service User and Support (SUS) questionnaire to collect other health and social care and out-of-pocket costs for clients in the MTB and the control group. The retrospective self-completed questionnaire will provide information on resources accessed during the last 6 months. The SUS will be completed at enrolment, 6 months after the baby is born by telephone and at each outcome assessment (infant age 1 and 2 years). Resource use will be costed using Personal Social Services Research Unit (PSSRU) and national datasets wherever possible

We will provide summary statistics of the costs for the MTB and the control group as well as a comparison of the total cost per patient to society of MTB compared to controls for the duration of the study.

Incremental cost-effectiveness ratio (ICER): the ICER is the mean cost per mother/child in the intervention minus the mean cost per patient in the control group divided by the mean incremental gain per mother/child in outcomes from the intervention compared to the controls. If an intervention has a lower cost to society and better outcomes it is considered dominant and likely to be adopted by a decision-maker if the evidence is satisfactory. If the intervention has higher cost to society but is associated with better outcomes the decision-maker needs adequate information to determine if they are willing to pay the additional cost per outcome gained.

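### MTB cost is assigned by practitioner caseload, not each family's recorded contacts, so the cost-effectiveness interval omits real variation; and no stated step keeps MTB visits out of the service-use costs

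*Protocol article*

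**What the plan says.** All references are to the Protocol article.

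- **Programme cost.** Under Economic evaluation, MTB is costed bottom-up, covering fixed running costs plus training, staffing and consumables. Each case then receives a weighted cost that depends on practitioner caseload. The family's own visits do not enter the rule.
- **Delivery data.** Under Intervention fidelity, practitioners record their direct and indirect contact with families and complete a form after each visit: "In particular practitioners record the length, nature and focus of the visit". The Minding the Baby section sets weekly visits to the first birthday and fortnightly visits to the second, and allows more visits in a crisis.
- **Other costs.** Under Economic evaluation, the SUS is used "to collect other health and social care and out-of-pocket costs for clients in the MTB and the control group". Under Secondary outcomes, the instrument is described more broadly: "Mothers are asked to note whether they had any input from professionals and voluntary agencies in the previous 6 months". It then adds: "Costs are applied to service use at each time point". Under Treatment as Usual, it also serves a second purpose; it "will be used to check what usual care services both groups of participants receive during the trial".
- **Who delivers MTB.** The team is "two qualified practitioners: a nurse or health visitor and a social worker". The Treatment as Usual section names health visitors, social workers and home-visiting services among usual care.
- **Interval.** Confidence limits for the incremental cost-effectiveness ratio (ICER) come from resampling the original data. A net-benefit acceptability curve is also planned.

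**The concern.** Cost-effectiveness is named as a key secondary aim, and both parts of the cost have a weakness.

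**Programme cost.** A caseload-based cost is the same for a family that left after a few visits and a family on the same caseload that had extra visits in a crisis. Families who leave the programme are to be kept in the research where possible (Scope of consent to participation), so both kinds will be in the data set. Resampling mothers cannot restore variation that was averaged out before the bootstrap. It also cannot restore the link between visits received and other service use or outcome. The interval and the acceptability curve then describe uncertainty in a cost that is partly smoothed.

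**Service-use cost.** A mother in the MTB arm who answers a question about any professional or voluntary-agency input can properly count her MTB visits. MTB practitioners share job titles with usual care, and no step is stated that removes their visits before unit costs are applied. A second count could arise in the MTB arm only. It would raise incremental cost, weigh against MTB in every planned ICER, and make MTB mothers appear to use more usual care.

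**Working it through.** The plan states no programme cost, unit cost, cost standard deviation or interval, so there is no figure to reproduce. The checks below show direction and possible size.

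**A. Caseload-based against by-family programme cost**

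1. *Mean.* If total programme cost T is divided over n families, the arm mean is T/n however T is shared among them. Averaging alone does not move the mean difference.

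2. *How much visits might vary.* For illustration, take the 15% dropout quoted for the UK FNP under Participant retention. Assume that those families stop at a uniformly random point among 90 planned visits (derived in B).
   - Mean = 0.85 × 90 + 0.15 × 45 = 83.25.
   - Mean square = 0.85 × 8100 + 0.15 × 2715 = 7292.25.
   - Variance = 7292.25 − 83.25² = 361.7, so SD = 19.0 and CV = 19.0/83.25 = 0.23.
   - Extra crisis visits and varying visit length would add to this. I assume a CV of 0.25 to 0.5.

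3. *Standard error of incremental cost.* Let n = 100 per arm (Participant retention). Let c be the CV of programme cost that averaging removes, s the SD of other costs in units of mean programme cost, and ρ their correlation. All three are assumptions.
   - Caseload-based: √(2s²/n).
   - By family: √[(c² + s² + 2ρcs)/n + s²/n].
   - Ratio: √[2s² / (2s² + c² + 2ρcs)]; n cancels.
   - Example: c = s = 0.5 and ρ = 0 gives √(0.50/0.75) = 0.82.
   - Example: c = 0.25, s = 1 and ρ = 0 gives √(2/2.0625) = 0.98.

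| c | s | ρ = −0.5 | ρ = −0.25 | ρ = 0 | ρ = 0.25 |
|---|---|---|---|---|---|
| 0.25 | 0.5 | 1.07 | 1.00 | 0.94 | 0.89 |
| 0.25 | 1.0 | 1.05 | 1.02 | 0.98 | 0.96 |
| 0.5 | 0.5 | 1.00 | 0.89 | 0.82 | 0.76 |
| 0.5 | 1.0 | 1.07 | 1.00 | 0.94 | 0.89 |

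   A ratio below 1 means the caseload-based standard error is too small. The ratio equals 1 at ρ = −c/(2s) and exceeds 1 when ρ is more negative than that, as when MTB visits displace other services.

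4. *Net benefit.* Its variance is λ²Var(E) + Var(C) − 2λCov(C,E), where λ is willingness to pay, E the outcome and C the cost. Caseload-based costing also drops the visit-related part of Cov(C,E). That covariance could be positive (more visits, better outcome) or negative (crisis families), so its effect on the acceptability curve could go either way.

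**B. Visits exposed to a second count**

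1. *Planned visits.* About 12 antenatal (assumed) + 52 in year 1 + 26 in year 2 = 90.
2. *Inside the 6-month recall windows.*
   - Secondary outcomes schedule (6, 12, 18 and 24 months): 26 + 26 + 13 + 13 = 78, and 78/90 = 87%.
   - Economic evaluation schedule (no 18-month wave): 26 + 26 + 13 = 65, and 65/90 = 72%.
3. *Share counted twice,* for an unknown share r of MTB visits reported on the SUS:

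| r | Secondary outcomes schedule | Economic evaluation schedule |
|---|---|---|
| 0 | 0% | 0% |
| 0.25 | 22% | 18% |
| 0.5 | 43% | 36% |
| 1 | 87% | 72% |

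These are shares of visits. They equal shares of programme cost only if the unit cost applied to a SUS contact matches the MTB cost per visit.

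**The case against.** **The plan separates the two cost elements.** The economic section reserves the SUS for other resources, and the Treatment as Usual section uses it to check usual care. The 36-item form is not shown and may already exclude MTB. This stands as far as it goes: a double count is a risk, not the plan. But the article's description of the form is broader than the economic section's intent, and no step joins the two.

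**Caseload costing is defensible.** Much of the cost is fixed or is training, and the weighted cost can differ between practitioners. A reader might call it one flat figure for all; the text does not support that. It still cannot vary with the visits that a family on a given caseload received.

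**Reported contacts could be adjusted later.** A reader might infer that MTB and usual-care contacts sharing a job title can never be separated. That goes too far, because the practitioner contact records would support an adjustment. The plan does not say that they will be used for it.

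**Changing the form is costly.** Recruitment began in April 2014 and protocol changes need a formal amendment. A new item on study home visits could also reveal allocation to assessors who must stay blind. This stands, and the fix avoids it.

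**Conclusion.** The point holds in limited form.

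*Interval.* Caseload-based costing leaves out between-family variation in programme cost and its covariance with other costs and outcomes. The standard error of incremental cost is likely, though not certainly, misstated. It is about 2–18% too small at ρ = 0 for an assumed c of 0.25–0.5 and s of 0.5–1. Over all the assumed values the ratio runs from 0.76 to 1.07. A reader might conclude that the interval is simply too narrow; the documents do not support that, because displacement of other services could make it too wide.

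*Mean.* A reader might also conclude that the incremental cost is biased. Averaging does not cause bias if the same total is spread over the same families. A double count would overstate MTB cost, but its size is unknown: from zero to a ceiling of about 87% of visits, or 72% on the economic section's schedule, with about 12 antenatal visits assumed.

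The analysis of the primary outcome is unaffected, although maternal sensitivity is one of the ICER denominators. The change is worth making because cost-effectiveness is a key secondary aim and the better data are already collected.

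**What to change.** 1. Cost MTB for each family as recorded contacts and visit length times the bottom-up unit cost, with fixed costs shared across families. Bootstrap these individual costs together with other costs and outcomes. The caseload-based cost can be kept as a sensitivity analysis.
2. State that MTB contacts are removed from SUS data before unit costs are applied. Economic staff who are not blind, and who are separate from the outcome assessors, should reconcile SUS-reported contacts with the MTB contact records for the same recall window. No new SUS item is needed. Apply the same cleaned data to the usual-care check.
3. Reconcile the SUS schedule: Secondary outcomes and Table 1 include 18 months, Economic evaluation does not. With 6-month recall, omitting that wave leaves months 12 to 18 uncosted in both arms.

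*Cost.* Some linkage of records already collected, and the cost-effectiveness interval may widen. Reconciling self-report with records will be imperfect, so results with and without the removal should both be shown.
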